### Statistical analyses

Three analysis sets will be used for analyzing data. First, a safety analysis set will be applied to analyze safety evaluation parameters. Safety analysis will be performed for a group of subjects who have ingested at least one treatment after random assignment. Second, a full analysis set will be applied, which refers to the ideal set of subjects as close as possible to the principle of intentionality analysis (including all of the subjects randomized to enroll and receive at least one treatment). Third, a per-protocol set will be applied when all of the factors are in accordance with the research plan; patients show good compliance using 80–120% of the prescribed dose. All of the baseline variables must be available, and there must be no major violation of the test plan.

For the primary endpoint, the degree of change of the VAS averaged after treatment from baseline will be analyzed using the paired *t* test or Wilcoxon signed rank test in each group. The difference between the groups will be analyzed with the two-sample *t* test or Wilcoxon rank sum test. Additionally, an analysis of covariance will be conducted with adjustments for covariates. Similar to the primary endpoint, the same analyses will be performed for the secondary endpoints. For categorical variables, the McNemar test will be carried out to evaluate the change from baseline in each group.

Demographic and clinical characteristics will be reported in terms of mean ± standard deviation for continuous variables, or as frequencies and percentages for categorical variables. Differences between groups will be analyzed using the two-sample *t* test or Wilcoxon rank sum test for continuous variables and the χ^2^ test or Fisher’s exact test for categorical variables.

AEs and adverse drug reactions will be tabulated for each treatment group in accordance with the system organ class and preferred terms of the Medical Dictionary for Regulatory Activities. The AEs and adverse drug reactions will then be classified according to severity, seriousness, and causal relationship to the study drug. Intergroup comparisons will be conducted using the χ^2^ test or Fisher’s exact test.

A value of *P* < 0.05 will be considered statistically significant. All analyses will be performed using SPSS Statistics software (v21.0; IBM Corporation, Armonk, NY, USA).

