### Sample size calculations

The enrolled participants will be randomly divided into two groups by at a 1:1 ratio. Under the assumption of 2.1 cm (with a pooled standard deviation of 2.4 cm) in the mean change difference in VAS values between the PG102P and placebo groups in a preceding pilot study with 0.9 of power, two-sided, and 0.05 of alpha, 28 participants will be allocated to each group. Considering a dropout rate of 30%, 80 participants will be needed (40 participants per group).

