Although we calculated the adequate sample size, the absolute number is quite small. The sample could potentially include relatively homogeneous patients so there might be a limitation in generalizing the results of our RCT to entire HD patient populations. Compared with cross-sectional designs, repeated measures designs allow the definitive evaluation of within-person changes over time and have higher statistical power for detecting differences. Thus, fewer participants are required for conducting a study. Most of the RCTs on uremic pruritus have traditionally used repeated measures designs [27].

In summary, the SNUG study is a multicenter, randomized, double-blind, placebo-controlled clinical trial that will evaluate the efficacy and safety of PG102P versus placebo in patients with chronic pruritus undergoing HD. This study is expected to confirm whether PG102P has an antipruritic effect.

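### The primary VAS comparison is unadjusted: it is valid and powered as planned, but making the baseline-adjusted comparison primary is a free improvement

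*Protocol article*

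**What the plan says.** The Statistical analyses section lists three steps for the primary endpoint. First, change from baseline is tested within each arm by a paired "test or Wilcoxon signed rank test in each group". Second, the arms are compared on that change: "The difference between the groups will be analyzed with the two-sample" t test or the Wilcoxon rank sum test. Third, "Additionally, an analysis of covariance will be conducted with adjustments for covariates". The secondary endpoints follow the same pattern.

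The sample size rests on the same unadjusted quantity, taken from a pilot study: "Under the assumption of 2.1 cm (with a pooled standard deviation of 2.4 cm) in the mean change difference in VAS values".

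Baseline VAS is available for everyone. The inclusion criteria and the section on the primary endpoint both make entry depend on an average VAS of about 4 or more over five days before the baseline visit. The Discussion, in defending the small sample, adds that "repeated measures designs allow the definitive evaluation of within-person changes over time and have higher statistical power for detecting differences".

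**The concern.** A change score subtracts the whole of the baseline value, as if each extra centimetre of itch at entry carried over in full to follow-up. In general it does not. When patients are selected for high recent itch, those who start highest tend to fall most whatever they receive. An arm that happens to start higher is then expected to show a larger fall, and the unadjusted comparison keeps that chance component as noise. ANCOVA estimates the carry-over from the data and removes it.

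At stake is the precision of the trial's main estimate, with 28 to 40 patients per arm. A smaller matter is that t and Wilcoxon are offered as alternatives, with no rule in the article for choosing between them.

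**Working it through.** **1. Reproduce the plan's sample size.** Inputs from Sample size calculations: difference 2.1 cm, SD 2.4 cm (read as the SD of the change score), two-sided alpha 0.05, power 0.90.

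n per group = 2 × (1.960 + 1.282)² × 2.4² / 2.1² = 2 × 10.51 × 5.76 / 4.41 = 27.4, rounded up to 28. With 30% dropout, 28 / 0.70 = 40 per group, 80 in total. Both stated figures reproduce. Power at 28 per group is 90.6% by the normal formula and 89.5% by the noncentral t. With all 40 per group analysed it is about 97%.

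**2. Variance with and without adjustment.** Let r be the baseline to follow-up correlation, k = baseline SD / follow-up SD, and s the follow-up SD.

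- Change score: s²(k² + 1 − 2rk)
- ANCOVA on baseline: s²(1 − r²)
- Ratio, ANCOVA to change score: (1 − r²) / (k² + 1 − 2rk)

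The two variances differ by s²(k − r)², which is never negative. In large samples ANCOVA is therefore never less precise, and the gain is zero only when r = k. At k = 1 the ratio reduces to (1 + r)/2.

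**3. Size of the gain.** The documents give neither r nor k, so both are assumed. Reduction in variance:

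| k | r = 0.3 | r = 0.5 | r = 0.7 |
|---|---|---|---|
| 0.5 | 4% | 0% | 7% |
| 0.7 | 15% | 5% | 0% |
| 1.0 | 35% | 25% | 15% |
| 1.2 | 47% | 40% | 33% |

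Example, k = 0.7 and r = 0.3: 0.91 / (0.49 + 1 − 0.42) = 0.91 / 1.07 = 0.85, a 15% reduction. On the standard error scale the k = 1 row is 1 − √0.65 = 19%, 1 − √0.75 = 13% and 1 − √0.85 = 8%.

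**4. In terms of power, for k = 1 only.** The effective SD is 2.4 × √((1 + r)/2), or 1.94, 2.08 and 2.21 cm at r = 0.3, 0.5 and 0.7. Power at 28 per group rises from 0.895 to about 0.98, 0.96 and 0.94. The number needed for 90% power falls from 28 to 18, 21 and 24 per group. Where the table shows no reduction, power stays at about 0.895.

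**5. Choosing between t and Wilcoxon after seeing the data.** A null simulation (normal data, k = 1, 28 or 40 per arm, r = 0.3, 0.5 and 0.7, 10,000 runs each) gave a type I error of 5.7% to 6.3% when the smaller of the two P values was taken. Each test alone gave 4.6% to 5.4%.

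**The case against.** The strongest reply is that nothing is wrong with the planned test. Under randomization a two-sample test on change is unbiased, it matches the quantity on which the trial was sized, and the promised power is there. That stands in full. The gain from adjustment may also be small. Entry at a VAS of about 4 or more narrows the baseline range, and eligibility uses a five-day average against three days at follow-up. Both could make the baseline SD the smaller one, and the k = 0.5 and 0.7 rows show how little might then be gained. ANCOVA also spends one residual degree of freedom (53 instead of 54 at 28 per arm), which is trivial.

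A reader might infer more than the text supports:

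- **A known loss of 15% to 35% of precision.** This is a variance figure for one assumed set of r values with equal SDs. The documents fix neither.
- **Three rival between-group P values.** Taking the smallest of t, Wilcoxon and ANCOVA would give about 7.5% to 9% type I error in the same simulation. But the protocol introduces ANCOVA as an addition, so it already ranks second. Only t against Wilcoxon is open. A rule for that choice, like the list of covariates, is something an article commonly leaves to the full protocol or SAP, so its absence here is no finding.
- **Within-group significance as the efficacy claim.** Suppose the drug has no effect and both arms of 40 share an assumed fall of 0.5, 0.75 or 1.0 cm (SD 2.4). The PG102P arm would be significant in 25%, 49% or 73% of trials. PG102P significant with placebo not would occur in 19%, 25% or 20%. That is a reason to report within-group changes descriptively. It does not show intent: the Abstract, Study design, Sample size calculations and Statistical analyses all specify a comparison with placebo.
- **A Discussion that contradicts the analysis.** The remark on repeated measures contrasts them with cross-sectional designs, and a change from baseline is a within-person measure. All that can be said is that the article names no longitudinal model.

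**Conclusion.** The point holds as a free improvement. The protocol puts the unadjusted comparison first and the adjusted one second, although the reverse order uses data already collected and, in large samples, is never less precise. The planned analysis is valid and adequately powered, so no result would be invalid if it were kept.

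The gain cannot be given as one number. Over assumed r of 0.3 to 0.7 it runs from essentially nothing to 47% of the variance as k goes from 0.5 to 1.2. These are large-sample formulas and take 2.4 cm as the SD of change. The inflation to about 6% from a free choice between t and Wilcoxon is modest and disappears once one test is named.

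**What to change.** Before unblinding, name a single primary between-group test in the protocol or SAP: ANCOVA of post-treatment VAS on treatment and baseline VAS, or a mixed model with the same baseline adjustment over the visits the protocol already defines. Leave the time points in the primary endpoint section (weeks 2, 4, 8 and 10) as they are, because covariate adjustment does not require changing the endpoint. Treat the continuous secondary endpoints in the same way, each with its own week-0 value as covariate.

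Keep the unadjusted t and Wilcoxon tests as sensitivity analyses. Report within-arm changes as estimates with confidence intervals, and do not offer them as evidence of efficacy.

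The cost is wording only. Baseline VAS is already collected, and neither the sample size nor any visit changes. The article reports 45 patients recruited at submission, which does not stand in the way as long as the blind is intact.

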### Randomization

Randomization will be performed by an independent statistician using a computerized random number generator through the block randomization method of SAS 9.3 software (SAS Institute, Cary, NC, USA). Eligible participants will be randomly assigned 1:1 to either a placebo group or a treatment group. All subjects eligible for selection/exclusion criteria at visit 2 (baseline visit, week 0) will be assigned to a group according to the allocation codes of the blocked randomization method. Each patient will be given a unique study number. An independent data manager who is not involved with the clinical practice or patient recruitment will create the randomization sequence. The practitioners, participants, outcome assessors, and statisticians will be kept blinded to treatment allocation throughout the trial. The randomization lists will be computer-generated and concealed from the investigators by an independent data manager not involved in the study. This information will remain confidential and will not be available to the researchers. In this trial, emergent unblinding is not applicable.

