## Discussion

This study will compare the changes in VAS between the PG102P and placebo groups in patients with uremic pruritus undergoing HD. The aim of PG102P treatment is to alleviate the itching sensation to improve the quality of life, including improving depression, insomnia, and ultimately the risk of mortality of patients.

Novel antipruritic drug development and research are actively ongoing. Naltrexone, a μ-opioid receptor antagonist, was investigated in a randomized control trial (RCT), but showed no effect and was accompanied by a high incidence of gastrointestinal side effects [21].

Nalfurafine, a κ-opioid receptor agonist, has been recently proven to effectively reduce itches that were refractory to current treatments with few significant adverse reactions in an RCT with 337 patients undergoing HD [22]. Nalfurafine was approved for clinical use by the Ministry of Health, Labour and Welfare of Japan in 2009. Nalfurafine seems to be potent, but it is expensive and currently prescribed only in Japan [13].

Pregabalin was examined in an RCT with 179 patients undergoing HD and was found to reduce VAS for pruritus by 6.6 cm at 12 weeks after starting the drug [23]. This reduction is remarkably larger than that seen with nalfurafine (4.2 cm at week 24 and 4.4 cm at week 52). A large-scale RCT is warranted in the future for validation.

PG102P is a water-soluble extract prepared from the edible fruit of *A. arguta*; therefore, safety problems are not an issue. A previous toxicity study showed that PG102P is a safe agent [16]. Moreover, in an RCT with 90 asymptomatic atopic dermatitis patients in 2011, no serious AEs were observed [24]. PG102P is also inexpensive.

We introduced VAS as a monodimensional scale for assessing pruritus intensity [25]. It is a simple method and has been validated in large-scale studies consisting of chronic pruritus patients, especially in RCTs of patients with uremic pruritus [10, 21–23]. It is highly reproducible and shows great correlation between scales. However, a VAS only provides the itch intensity at a specific point in time, and is susceptible to cofounding factors such as current mood, stress and comorbidities. Multidimensional scales, such as the Itch Severity Scale [26], a self-reported seven-item scale, are an alternative method. They provide comprehensive scores of itch intensity, sleep disturbance and burden by the symptom, but are not established in clinical practice.

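### Adverse events are compared between arms only by chi-square or Fisher tests at P<0.05; at 40 per arm these have low power and can disagree, so report risk differences with 95% confidence intervals

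*Protocol article*

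**What the plan says.** The Statistical analyses section of the protocol article plans adverse events and adverse drug reactions in three steps. They are tabulated for each arm by MedDRA system organ class and preferred term, classified by severity, seriousness and causal relationship, and then tested: "Intergroup comparisons will be conducted using the" chi-square or Fisher's exact test. Later in the section, one threshold is set for the whole analysis: a P value below "0.05 will be considered statistically significant". No exemption is made for safety, no rule says when each test applies, and no risk difference or confidence interval is mentioned for adverse events.

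The safety population is defined by exposure: "Safety analysis will be performed for a group of subjects who have ingested at least one treatment after random assignment".

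The Sample size calculations section sizes the trial on itch alone: "Under the assumption of 2.1 cm (with a pooled standard deviation of 2.4 cm) in the mean change difference in VAS values". It reaches 28 per arm, and 40 per arm after allowing for 30% dropout. No detectable adverse event rate is stated. Safety stands in the article's title, and the summary that closes the Discussion promises an evaluation of efficacy and safety.

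**The concern.** A significance test answers whether an excess of events is distinguishable from zero at the 5% level. A safety evaluation needs to know how large an excess the data still allow. With 40 per arm these questions come apart, because an excess that would matter to patients can easily return P≥0.05.

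The two named tests can also disagree on the same sparse table, so the reported result may depend on which is run. At stake is what the trial can say about harm: "no significant difference", or an estimated excess with limits.

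**Working it through.** **Inputs.** 40 per arm with 1:1 allocation (Sample size calculations; Randomization). Chi-square or Fisher test, P<0.05 (Statistical analyses); two-sided P values are used below. The true event rates are my assumptions, since the article gives none. The safety set is taken as the full 40 per arm, the most it would hold if recruitment meets the target.

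**The plan's own figure.** n per arm = 2(1.960 + 1.282)² × 2.4² / 2.1² = 27.4, rounded up to 28. Then 28 / 0.70 = 40. The stated sample size reproduces. It concerns VAS only.

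**One table, two tests: 5/40 versus 0/40.**
- Fisher, two-sided: 2 × C(40,5) / C(80,5) = 2 × 658,008 / 24,040,016 = 0.0547.
- Pearson chi-square, uncorrected: 80 × (5×40 − 35×0)² / (40 × 40 × 5 × 75) = 5.33, P = 0.0209.
- Chi-square with Yates correction: P = 0.0647.
- Smallest expected count: 5 × 40/80 = 2.5. The usual convention would choose Fisher here, but the article does not state it.

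**Smallest PG102P count giving P<0.05.**

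| Placebo | Fisher | Pearson |
|---|---|---|
| 0/40 | 6/40 (P=0.026) | 4/40 (P=0.040) |
| 1/40 | 8/40 (P=0.029) | 6/40 (P=0.048) |
| 2/40 | 9/40 (P=0.048) | 8/40 (P=0.043) |

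The Fisher result is also sensitive to one patient: 5/39 versus 0/40 gives P=0.026.

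**Power at 40 per arm.** This is the sum of Bin(a; 40, p₁) × Bin(b; 40, p₀) over all tables (a, b) with P<0.05.

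| True rates, PG102P v placebo | Fisher | Pearson |
|---|---|---|
| 15% v 5% | 18% | 35% |
| 20% v 5% | 41% | 57% |
| 12.5% v 0% | 38% | 75% |

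**What an interval would show (Newcombe, from Wilson limits).**
- 5/40 versus 0/40: the Wilson limits are 5.5% to 26.1% and 0% to 8.8%. The difference is 12.5 points. The lower limit is 12.5 − √[(12.5−5.5)² + (8.8−0)²] ≈ 1.3, and the upper limit is 12.5 + √[(26.1−12.5)² + 0²] ≈ 26.1 points.
- 6/40 versus 2/40, the expected counts at 15% versus 5% (40 × 0.15 = 6; 40 × 0.05 = 2): Fisher P=0.26, Pearson P=0.14. The Wilson limits are 7.1% to 29.1% and 1.4% to 16.5%. The difference is 10 points, with limits 10 − √[(15−7.1)² + (16.5−5)²] ≈ −4.0 and 10 + √[(29.1−15)² + (5−1.4)²] ≈ 24.5 points. Both tests are non-significant, yet an excess of more than 20 points remains compatible with the data.
- 0/40 in one arm: the one-sided 95% upper limit is 1 − 0.05^(1/40) = 7.2%.

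**The case against.** The strongest reply is that this is a condensed journal article. Interval estimates and the rule for choosing between two tests are often left to the analysis plan, which is not shown. That carries weight and is why the point is modest. It does not remove it, because the article does not leave the comparison open: it names the tests and sets a threshold that covers them.

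Second, low power for adverse events follows from sizing on VAS, and the Discussion concedes that the sample is quite small. This is true, and intervals add no power. They do make the remaining uncertainty visible.

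Third, the tables by arm already show the counts, so a 5 versus 0 imbalance would be seen whatever the P value. This stands. The tests are the only stated between-arm inference, but they are not the only safety information.

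Three stronger readings are tempting, and the documents do not support them:
- That a 5/40 versus 0/40 harm would be declared non-significant under the plan. This holds for Fisher and for the Yates-corrected chi-square, but not for the uncorrected Pearson test.
- That the safety comparison would shrink to 28 per arm after dropout. The safety set keeps everyone who took at least one dose, so patients who leave after dosing stay in.
- That the investigators will read P≥0.05 as evidence of safety. Nothing says so. The Discussion's remark that "safety problems are not an issue" is argued from the product's edible-fruit origin, a toxicity study and an earlier randomized trial, not from this trial's tests.

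**Conclusion.** The point holds as an inexpensive improvement to the stated analysis. The article's only stated between-arm inference on harms is a significance test that, at 40 per arm, misses a tripling of an event rate from 5% to 15% in 82% of trials with Fisher (100 − 18) and 65% with Pearson (100 − 35). In sparse tables such as 5 versus 0 the two permitted tests fall on opposite sides of 0.05. A non-significant P value would therefore say little about safety.

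The figures assume two-sided tests, 40 treated patients per arm and the illustrative event rates shown. A smaller safety set would generally lower the power further. The planned tabulation limits the damage, and there is no numerical error or internal contradiction.

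**What to change.** Alongside the planned counts and percentages per arm in the safety set, report the risk difference (PG102P minus placebo) with its 95% confidence interval for any adverse event, serious events, drug-related events and each system organ class. Name an interval method that copes with zero counts, such as Newcombe's. Treat any P values for adverse events as descriptive and state which test produced them. Say that the safety statement rests on the confidence limits and that P≥0.05 is not evidence of safety.

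The cost is a sentence or two in the analysis plan and a few table columns, with no new data and no change to trial conduct. The downside is that the intervals will be wide and the safety statement less favourable.

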## Discussion

This study will compare the changes in VAS between the PG102P and placebo groups in patients with uremic pruritus undergoing HD. The aim of PG102P treatment is to alleviate the itching sensation to improve the quality of life, including improving depression, insomnia, and ultimately the risk of mortality of patients.

Novel antipruritic drug development and research are actively ongoing. Naltrexone, a μ-opioid receptor antagonist, was investigated in a randomized control trial (RCT), but showed no effect and was accompanied by a high incidence of gastrointestinal side effects [21].

Nalfurafine, a κ-opioid receptor agonist, has been recently proven to effectively reduce itches that were refractory to current treatments with few significant adverse reactions in an RCT with 337 patients undergoing HD [22]. Nalfurafine was approved for clinical use by the Ministry of Health, Labour and Welfare of Japan in 2009. Nalfurafine seems to be potent, but it is expensive and currently prescribed only in Japan [13].

Pregabalin was examined in an RCT with 179 patients undergoing HD and was found to reduce VAS for pruritus by 6.6 cm at 12 weeks after starting the drug [23]. This reduction is remarkably larger than that seen with nalfurafine (4.2 cm at week 24 and 4.4 cm at week 52). A large-scale RCT is warranted in the future for validation.

PG102P is a water-soluble extract prepared from the edible fruit of *A. arguta*; therefore, safety problems are not an issue. A previous toxicity study showed that PG102P is a safe agent [16]. Moreover, in an RCT with 90 asymptomatic atopic dermatitis patients in 2011, no serious AEs were observed [24]. PG102P is also inexpensive.

We introduced VAS as a monodimensional scale for assessing pruritus intensity [25]. It is a simple method and has been validated in large-scale studies consisting of chronic pruritus patients, especially in RCTs of patients with uremic pruritus [10, 21–23]. It is highly reproducible and shows great correlation between scales. However, a VAS only provides the itch intensity at a specific point in time, and is susceptible to cofounding factors such as current mood, stress and comorbidities. Multidimensional scales, such as the Itch Severity Scale [26], a self-reported seven-item scale, are an alternative method. They provide comprehensive scores of itch intensity, sleep disturbance and burden by the symptom, but are not established in clinical practice.

Although we calculated the adequate sample size, the absolute number is quite small. The sample could potentially include relatively homogeneous patients so there might be a limitation in generalizing the results of our RCT to entire HD patient populations. Compared with cross-sectional designs, repeated measures designs allow the definitive evaluation of within-person changes over time and have higher statistical power for detecting differences. Thus, fewer participants are required for conducting a study. Most of the RCTs on uremic pruritus have traditionally used repeated measures designs [27].

In summary, the SNUG study is a multicenter, randomized, double-blind, placebo-controlled clinical trial that will evaluate the efficacy and safety of PG102P versus placebo in patients with chronic pruritus undergoing HD. This study is expected to confirm whether PG102P has an antipruritic effect.

